## Abstract

**Background:**

Reducing the rates of sexually transmitted infections (STIs) among young people is a public health priority. The best way to avoid STIs from penetrative sex is to use a condom, but young people report inconsistent use. A missed opportunity to intervene to increase condom use is when young people access self-sampling kits for STIs through the internet. The potential of this opportunity is enhanced by the increasing numbers of young people being tested through this route every year in England. Hence, in a cocreation by young people, stakeholders, and researchers, Wrapped was developed––a fully automated, multicomponent, and interactive digital behavior change intervention developed for users of STI self-sampling websites, who are aged 16-24 years.

**Objective:**

This paper is a protocol for a feasibility randomized controlled trial (fRCT). The fRCT seeks to establish whether it is feasible to run a randomized controlled trial to test the effectiveness and cost-effectiveness of Wrapped. Wrapped aims to reduce the incidence of STIs through increasing correct and consistent use of condoms among users of STI self-sampling websites, who are aged 16-24 years.

**Methods:**

A 2-arm parallel-group randomized fRCT of Wrapped plus usual care, compared to usual care only (basic information on STIs and condom use), with a nested qualitative study. A minimum of 230 participants (aged 16-24 years) are recruited from an existing chlamydia self-sampling website. Participants are randomized into 1 of 2 parallel groups (1:1 allocation). Primary outcomes are the percentage of users recruited to the fRCT and the percentage of randomized participants who return a chlamydia self-sampling kit at month 12. Additionally, besides chlamydia positivity based on biological samples, surveys at baseline, month 3, month 6, and month 12, are used to assess condom use attitude, behavioral capability, self-efficacy, and intention, along with details of any partnered sexual activity and condom use, and health economic data. Nested qualitative interviews with trial participants are used to gain insight into the factors affecting recruitment and attrition.

**Results:**

Recruitment to the fRCT began in March 2021 and was completed in October 2021. Data collection was completed in December 2022.

**Conclusions:**

This feasibility study will provide data to inform the design of a future-definitive trial. This work is timely given a rapid rise in the use of internet testing for STIs and the sustained high levels of STIs among young people.

**Trial Registration:**

ISRCTN Registry ISRCTN17478654; http://www.isrctn.com/ISRCTN17478654

**International Registered Report Identifier (IRRID):**

DERR1-10.2196/43645

## Introduction

### Background and Rationale

Sexually transmitted infection (STI) diagnoses in England have been persistently high over the past decade [1]. Although the most recent annual data show a 32% reduction in STI diagnoses, down from a 10-year high of 467,096 in 2019 to 307,901 in 2020, this likely reflects a temporary shift brought about by the COVID-19 pandemic, which placed restrictions on public behavior and reduced access to STI testing [1,2]. Young people continue to carry a high burden of infection, with 46% of all new diagnoses among 15- to 24-year-olds [1]. Furthermore, women, those of Black ethnicity, those living in the most deprived areas, and men who have sex with men, remain disproportionately affected [1]. Among young people, chlamydia continues to be the most prevalent STI [1]. Rates of chlamydia among 15- to 24-year-olds have been high but stable over recent years, whereas increases have been observed for other STIs, such as gonorrhea and syphilis [2]. The removal of COVID-19 restrictions and an increase in testing availability will likely bring with it a return to prepandemic levels of STI diagnoses and as such, sexual health continues to be a public health concern [1]. Untreated STIs can lead to serious health consequences, such as pelvic inflammatory disease, ectopic pregnancy, and infertility, which have a significant impact on health and quality of life [3]. The estimated annual cost to the National Health Service (NHS) of STI treatment is £620 (US $762.6) million [4]. The best way to avoid STIs from penetrative sex is to use a condom [5], but young people report inconsistent use [6,7].

Although condom use is the cornerstone of STI prevention, STI testing is important for treatment and to prevent onward transmission. There have been notable changes in the landscape of STI testing within England since 2017. In the period between 2017 and 2019, against a backdrop of increasing testing overall, there was a shift toward the use of internet services, and away from other nonspecialist services [8]. Between 2018 and 2019, while the number of tests carried out by specialist sexual health services (eg, genitourinary medicine services) remained relatively stable, those carried out by nonspecialist services (excluding internet testing), such as pharmacies, general practice, and community-based settings, decreased by 9%, and those by internet services increased by 69% [8]. This trend reflects recent year-on-year increases, with internet testing accounting for 4% of all testing in 2017, 13% in 2018, and 19% in 2019 [8]. The global COVID-19 pandemic has further served to accelerate the move in this direction across Europe [9,10]. In England, despite there being a reduction of 30% in expected levels of chlamydia testing in 2020, a 2-fold increase in internet testing was observed, with approximately 40% of all chlamydia testing being processed through the internet in 2020 [1]. Whether internet testing remains at these elevated levels or begins to adjust back toward those observed prepandemic, remains to be seen. Regardless, internet testing is now an established and significant route to STI diagnosis and treatment within England.

Evidence indicates that STI self-sampling websites are effective at reaching higher prevalence groups; chlamydia positivity is comparable to that of other nonspecialist services [8], and they attract equivalent numbers of males and females, and those from across the spectrum of deprivation ([name], unpublished data, 2017). Repeated use of internet testing services is however common, with chlamydia positivity remaining high for those that retest ([name], unpublished data, 2017), suggesting that testing online does not reliably translate into future individual prevention efforts. Furthermore, while information on STIs and contraceptive methods is typically found on self-sampling websites, this is insufficient for behavior change [11], and inconsistent with Public Health England guidance to provide those at elevated risk of STIs with preventative intervention [12]. As such, self-sampling websites provide an important but currently missed opportunity to intervene with a priority group.

In 2016-2017, with the support of Medical Research Council Public Health Intervention Development funding and in line with Medical Research Council guidance on the development of complex interventions [13], Wrapped was cocreated by young people, stakeholders, and researchers [14]. Wrapped is a fully automated, multicomponent, and interactive digital intervention developed for the users of STI self-sampling websites aged 16-24 years. It aims to reduce the incidence of future STIs by increasing correct and consistent use of condoms for penetrative sex. The users of STI self-sampling websites can be signposted to Wrapped upon order of an STI self-sampling kit (through a hyperlink). Content is tailored, with between 1 and 6 different components allocated to users in accordance with their self-identified barriers to condom use. These barriers reflect important behavioral determinants of condom use identified through existing meta-analyses [15-18], namely condom use attitudes (particularly beliefs around pleasure, enjoyment, and spontaneity), condom availability, and behavioral capability and self-efficacy for condom use and communication.

In 2019, funding was awarded by the National Institute for Health and Care Research Public Health Research program to determine whether it is feasible to run a randomized controlled trial (RCT) to test the effectiveness and cost-effectiveness of Wrapped. This paper presents the protocol for this feasibility randomized controlled trial (fRCT).

### Aim and Objectives

The aim of this study is to assess whether and how it is possible to carry out a future definitive RCT to evaluate the effectiveness and cost-effectiveness of Wrapped plus usual care, in comparison to usual care only.

The primary objectives are to estimate the following parameters for planning a definitive RCT:

The rate of recruitment of eligible participants.The rate of participant follow-up for the definitive RCT primary outcome measure (chlamydia positivity at 12 months measured using biological samples).

The secondary objectives are as follows:

Estimate the rate of participant follow-up for the definitive RCT secondary outcome measure chlamydia cumulative incidence.Identify whether the level of deprivation of the final sample is representative of web-based STI self-sampling users.Identify whether differential retention occurs across groups (gender, ethnicity, sexual identity, deprivation, randomized groups, and chlamydia diagnosis at baseline).Measure chlamydia positivity at 12 months in the intervention and control groups (to support sample size calculation for the definitive RCT).Identify the rate of attrition at 3 months, 6 months, and 12 months, and ways of minimizing this.Determine the feasibility and participant acceptability of all primary and secondary outcome measures (including health economic measures).Identify which recruitment messages result in the highest rate of recruitment.Identify and remove the intervention “friction points” (using web analytics data) to minimize attrition and maximize the future intervention dose.Identify costs and resource use associated with the intervention for health care services and users (to inform the design of the definitive RCT and the future economic evaluation).Measure contamination of intervention effect in the control group.Identify possible adverse effects of the intervention, for example, participants’ inadvertent disclosure that they are testing for an STI or increase in consumption of pornography.

### Study Design

A 2-arm parallel group fRCT of Wrapped plus usual care compared to usual care alone with a nested qualitative study.

## Methods

Please refer to Multimedia Appendix 1 for a visual representation of the study design, recruitment process, and timing of measures based on the Consolidated Standards of Reporting Trials (CONSORT) extension for pilot and feasibility trials [19].

### Study Population and Setting

Recruitment, intervention delivery, and data collection are conducted entirely on the internet. Participants will be recruited from an existing chlamydia self-sampling website (freetest.me [20]). Freetest.me provides a web-based chlamydia testing service to local authority areas across England (typically subcontracted to and administered through NHS trusts) and is free at the point of use. For the purposes of this study, users of freetest.me residing in 1 of 4 local authority areas will be invited to participate.

### Eligibility Criteria

The inclusion and exclusion criteria are outlined in Textbox 1.

Inclusion and exclusion criteria.
**Inclusion criteria:**
Aged 16-24 years.Living in a local authority area participating in the study.
**Exclusion criteria:**
No internet access.Sexual activity does not typically include penetrative sex (penis in vagina or anus).

### Participant Timeline

Table 1 gives an overview of participant activities and timing.

To recompense for time spent in completing activities, participants will receive payment in the form of vouchers (see Multimedia Appendix 2 for the schedule of payments).

**Table 1 table1:** Participant activities across the duration of the study.

Activity	M0^a^	M3^b^	M6^c^	M12^d^
Read participant information	✓			
Complete consent	✓			
Complete survey	✓	✓	✓	✓
Self-report chlamydia test result	✓			
Complete chlamydia self-sample		✓		✓

^a^M0: month 0.

^b^M3: month 3.

^c^M6: month 6.

^d^M12: month 12.

### Recruitment

A study invitation will be placed on the “thank you” page of the freetest.me website displayed to users after they have placed an order for a chlamydia self-sampling kit. Every 2 weeks, the advert will change to emphasize a different value proposition (see Multimedia Appendix 3 for the list of adverts). A hyperlink within the advert will take users to Research Electronic Data Capture (REDCap), a secure data capture and management platform, for participant information and consent (see Multimedia Appendix 4 for a copy of the participant information and consent form). Each individual’s freetest.me order number will be appended to the URL. This order number will be captured by REDCap enabling the research team to ensure that each participant is a unique and genuine user of freetest.me.

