### Secondary Outcome Measures

Secondary outcome measures are as follows:

Percentage of randomized participants with outcome data required to measure cumulative incidence of chlamydia (measured using M3 and M12 chlamydia self-sample, and the relevant item within M3, M6 and M12 surveys).The distribution of Index of Multiple Deprivation quintile among users of freetest.me over the 3-month recruitment period, compared to that of the final sample, within each of the 4 recruitment areas.The number of randomized participants with a valid primary outcome measure at M12 by group (gender, ethnicity, sexual identity, deprivation, randomized groups, and chlamydia diagnosis at baseline).The number of randomized participants testing positive for chlamydia at M12 in the intervention and the control group.Attrition curves comparing the percentage of valid participants in the trial at randomization, M3, M6, and M12 plotted for the intervention and control arms (dropout attrition).Completeness of data from outcome measures that would be needed in a definitive trial (ie, self-report of chlamydia result at baseline, results from biological samples, demographic information, self-report of condom use and chlamydia infection, and data needed for cost-effectiveness and cost-utility analyses).The percentage of freetest.me users randomized following each of the different recruitment messages employed.The percentage of valid participants in the 2 arms that do not achieve predetermined intervention “goals” (ie, do not follow instructions within each component of the Wrapped website to their culmination, for example, ordering a sample pack, or watching a suggested video), and the bounce rate for home and content pages.Completeness of data on costs and resource use that would be needed for the economic evaluation in the definitive RCT.Proportion of participants in the control group who report (at M12) any exposure to Wrapped.The total number of adverse events reported during the course of the study (inadvertent disclosure that sexually active or testing for STI if overseen using Wrapped, initiation or change in the consumption of pornography, or other).

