#### Statistical Analysis

Researchers performing the analysis (KN, KB, LJ, and SB) will be blinded to participant allocation. Quantitative data will be analyzed descriptively. Measures of location and dispersion, including means and SDs, medians and IQRs, and number and percent for categorical variables, will be used to describe the data at baseline and at each follow-up time point. CIs will be calculated and presented as appropriate. All analyses will be performed using SPSS (version 28; IBM Corp). As with the raw data, the syntaxes used for analysis and the output generated will also be deposited within the UHRA and made available indefinitely on an open-access basis.

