The unusual context in which this fRCT is being run should be acknowledged. The COVID-19 pandemic has affected sexual health services and sexual behavior in ways that could not have been imagined at the time this study was conceived. When recruitment to the fRCT was initiated, restrictions on public behavior imposed to control the spread of infection were still in place but were lifted approximately 3 months later. The impact of the environment at that time on STI testing and diagnoses will not be known until the release of annual STI data in Autumn 2022. Although an increase in the use of internet testing will serve to increase the size of the sampling pool drawn upon for this study, thus potentially accelerating recruitment, it should not impact upon the recruitment rate, as this is merely a reflection of the rate at which those who see the advert are converted into participants. It should, however, be acknowledged that the pandemic is likely to have both positively and negatively impacted on people’s time and/or willingness to engage in research, factors which for some will also have changed with changing restrictions and may serve to influence study recruitment and retention. It is also important to consider whether changes in sexual risk behavior during this time could lead to fewer cases of chlamydia being identified in the present study than anticipated. This concern is, however, not supported by community surveys, which indicate that a substantial proportion of people continued to engage in at-risk behavior during 2020 [28-30], and the most recent STI data which shows that among those seeking internet testing, chlamydia positivity was comparable between 2019 (23,426/284,050, 8.2%) and 2020 (33,294/381,744, 8.7%) [1].

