## Appendix

Multimedia Appendix 1 Wrapped CONSORT Diagram.

Multimedia Appendix 2 Schedule of voucher payments.

Multimedia Appendix 3 Advert schedule.

Multimedia Appendix 4 Participant information and consent.

Multimedia Appendix 5 Survey items.

Multimedia Appendix 6 Intervention logic model.

Multimedia Appendix 7 Analytics data measurements.

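### Recruitment adverts are rotated in two-week blocks rather than shown concurrently, so the ranking of messages is open to confounding by calendar time and cannot reliably identify the best one

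*Protocol article*

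**What the plan says.** Under Recruitment, the study invitation sits on the page shown after a user orders a kit, and its content is rotated by calendar time: "Every 2 weeks, the advert will change to emphasize a different value proposition". The article describes neither concurrent display nor random choice of advert. The same section says that each user's order number is appended to the link into the data capture system.

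Aim and Objectives lists as a secondary objective: "Identify which recruitment messages result in the highest rate of recruitment". The matching entry under Secondary Outcome Measures is "The percentage of freetest.me users randomized following each of the different recruitment messages employed". Strengths and Limitations names the choice of advertisement among the matters the study should settle for the future trial. Under Statistical Analysis, "Quantitative data will be analyzed descriptively", with confidence intervals as appropriate.

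On timing, Results states: "Recruitment to the fRCT began in March 2021 and was completed in October 2021". Secondary Outcome Measures refers to users "over the 3-month recruitment period". Strengths and Limitations says restrictions were in force when recruitment opened and were lifted about 3 months later. It adds that the pandemic probably altered how able and ready people were to join a study: "factors which for some will also have changed with changing restrictions and may serve to influence study recruitment and retention". That section does not connect this to the advert comparison.

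The adverts are listed in an appendix that is not shown ("Multimedia Appendix 3 Advert schedule"). The number of messages and any repeats are therefore unknown here.

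**The concern.** No two messages are ever on display in the same fortnight. A difference in conversion between two messages may come from the messages, from the periods in which they ran, or from both. The protocol names a plausible period effect that falls inside the actual recruitment window, and the article describes nothing that would separate it from the effect of the message.

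What is at stake is the choice of advert for the definitive trial. A message that happened to run in a favourable fortnight could be preferred to a better one, and its observed rate would flatter it.

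**Working it through.** **Inputs from the protocol.** One advert at a time, changed every 2 weeks (Recruitment). Actual window March to October 2021 (Results). Planned window 3 months (Secondary Outcome Measures). Restrictions lifted about 3 months after the start (Strengths and Limitations). Total sample 230 (Sample Size).

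**Inputs assumed.** Number of messages, number of repeats, true advantage of the best message, and size of the period effects. The documents give none of these.

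**1. The plan's own figure.** 60/0.75 = 80; 80/0.7 = 114.3, rounded up to 115 per arm; 2 × 115 = 230. The total reproduces. No sample size is stated for the advert comparison.

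**2. Number of blocks.**
- Longest reading of the actual window, 1 March to 31 October: 34.9 weeks, 34.9/2 = 17.4 blocks, 230/17.4 = about 13 recruits per block.
- Shortest reading, 31 March to 1 October: 26.3 weeks, 13.1 blocks, about 17.5 recruits per block.
- Planned 3 months: about 13 weeks, 6.5 blocks, about 35 recruits per block.

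**3. Can message and time be separated?** Take a model with one indicator per message plus time terms.
- Six messages run once each, with one step or one linear time term: rank 6 for 7 columns. No analysis can separate message from time.
- Six messages run twice, with one such term: rank 7 of 7.
- Four, six or eight messages cycled over 16 blocks, with a step and a linear trend: full rank (6 of 6, 8 of 8, 10 of 10).

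So confounding is complete if each advert ran once. If adverts recurred it is partial, and smooth trends can be adjusted for.

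**4. Size under independent fortnight effects.** Simulation: 230 recruits in expectation, Poisson counts, a lognormal effect for each block, one message with rate ratio 1.3, and the message with the highest crude rate chosen. Chance that the truly better message ranks first:

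| Design | No period effect (equivalent to concurrent display) | CV 20% | CV 30% |
|---|---|---|---|
| 6 messages, one block each | 68% | 47% | 38% |
| 6 messages, two blocks each | 68% | 54% | 46% |
| 4 messages, four blocks each | 84% | 74% | 66% |

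If six messages run once each and are equally good, the median ratio of the best to the mean is 1.20 from sampling noise alone and 1.32 at CV 20%. The ratio of best to worst is 1.5 and 1.9.

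**5. Size under a single step change.** 16 blocks, rate ratio 1.3, conversion multiplied by 0.7 to 1.5 when restrictions lift. With 4 messages the better one is picked 83% of the time with no step, 57% to 71% if each runs in one contiguous stretch, and 80% to 83% if they are cycled. With 8 messages the figures are 54% to 55%, 41% to 48% and 50% to 54%. Cycling protects well against one step, but less well against the fortnight-to-fortnight variation in item 4.

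**6. Precision apart from confounding.** For two blocks with n recruits each, the rate ratio detectable with 80% power is exp(2.80 × √(2/n)): 3.0 for n = 13, 2.6 for n = 17 and 1.95 for n = 35.

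**The case against.** Five counter-arguments deserve weight.

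**The schedule is not shown.** A reader might infer that each message ran about once and that the best message therefore cannot be identified at all. The documents do not support that. The planned 3 months gives only about six fortnights, but the actual window gives 13 to 17, enough for repeat cycles. Nor should the few blocks of the planned window be combined with a lifting of restrictions that falls at about its end; that change lies well inside only the longer, actual window. This limits the point to lack of reliability. It does not remove it, because adverts shown in turn are never concurrent.

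**The outcome is a rate.** Strengths and Limitations argues that a larger pool of testers should not alter the conversion rate. That is right for volume, which is in the denominator. It does not cover changes in willingness, which the same paragraph concedes, or in the mix of users.

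**Small numbers matter as much.** Even with concurrent display, a message 30% better ranks first in only 68% of runs with six messages. This stands: concurrent display removes the bias but not the noise.

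**Adjustment may be in an analysis plan.** It may, and the lack of a described time adjustment is not a fault of the article. But if each advert ran once, no adjustment can work. If they recurred, adjustment handles smooth trends better than irregular fortnight effects.

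**The objective is minor.** It is one of eleven descriptive secondary objectives. A reader might infer that an inflated message-specific rate would feed the first progression criterion. Progression Criteria bases that criterion on the overall proportion of users recruited, and nothing in the document carries a single message's rate into it.

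**Conclusion.** The concern holds in a limited form. As described, the comparison of messages is non-concurrent and open to confounding by calendar time, in a window where the protocol itself expects willingness to take part to have shifted. The ranking cannot reliably identify the best message.

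With six messages and period CVs of 20% to 30%, the chance of picking a truly 30% better message falls by 21 to 30 percentage points if each runs once (68% to 47% or 38%), and by 14 to 22 points if each runs twice (68% to 54% or 46%). These figures rest on an assumed number of messages and assumed period effects. They show the order of magnitude and do not estimate what happened.

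The consequence is confined to the choice of advert for the definitive trial. The overall recruitment percentage, the first progression criterion and the randomized comparison are not affected. The change is worth making, but the trial's main purpose does not depend on it.

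**What to change.** - **Preferred design.** Choose the advert at random for each completed order, and append an advert ID to the link that already carries the order number. Report the number randomized over the number exposed for each message, with confidence intervals.
- **If the provider's site cannot do this.** Rotate adverts at short intervals in a repeated random order, and compare messages within period.
- **Where the two-week blocks have already been run.** Report rates by message and by fortnight with their denominators, state that message and period are confounded to the extent the schedule implies, and present the ranking as exploratory. Test the messages concurrently before or within the definitive trial.

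The cost is a small change to the provider's web page and one extra link parameter, with no additional participants. Whether the provider can support it is not stated in the protocol and would need to be confirmed. Reporting by fortnight needs only the date and advert for each exposed user.
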